## Abstract

**Background:**

Postoperative delirium is common in the elderly and is associated with a significant increase in mortality, complications, length of hospital stay and admission in long care facility. Although several interventions have proved their effectiveness to prevent it, the Cochrane advises an assessment of multifaceted intervention using rigorous methodology based on randomized study design. Our purpose is to present the methodology and expected results of the CONFUCIUS trial, which aims to measure the impact of a multifaceted program on the prevention of postoperative delirium in elderly.

**Method/Design:**

Study design is a stepped wedge cluster randomized trial within 3 surgical wards of three French university hospitals. All patients aged 75 and older, and admitted for scheduled surgery will be included. The multifaceted program will be conducted by mobile geriatric team, including geriatric preoperative consultation, training of the surgical staff and implementation of the *Hospital Elder Life Program*, and morbidity and mortality conference related to delirium cases. The primary outcome is based on postoperative delirium rate within 7 days after surgery. This program is planned to be implemented along four successive time periods within all the surgical wards. Each one will be affected successively to the control arm and to the intervention arm of the trial and the order of program introduction within each surgical ward will be randomly assigned. Based on a 20% reduction of postoperative delirium rate (ICC = 0.25, α = 0.05, β = 0.1), three hundred sixty patients will be included i.e. thirty patients per service and per time period. Endpoints comparison between intervention and control arms of the trial will be performed by considering the cluster and time effects.

**Discussion:**

Better prevention of delirium is expected from the multifaceted program, including a decrease of postoperative delirium, and its consequences (mortality, morbidity, postoperative complications and length of hospital stay) among elderly patients. This study should allow better diagnosis of delirium and strengthen the collaboration between surgical and mobile geriatric teams. Should the program have a substantial impact on the prevention of postoperative delirium in elderly, it could be extended to other facilities.

**Trial registration:**

ClinicalTrials.gov: NCT01316965

## Background

Postoperative delirium is a common acute disorder of attention and cognition, which can cause serious health concern among the elderly [1]. After hip-fracture repair, its incidence ranges from 26 to 52% [2-4]. Inpatient's delirium is associated with an increase in postoperative complications and mortality, risk of functional decline, dementia, length of hospital stay, hospital costs and rates of nursing home placement on discharge [5-11].

The impact of prevention program of delirium has been assessed in general medicine or in surgical ward. However published studies in surgical wards were focused on orthopaedic care and assessed mainly pharmacological interventions [12-14]. Yet, pharmacological interventions did not show evidence to prevent delirium in elderly [13]. Conversely, there is now increasing evidence that delirium can be prevented through non-pharmacological interventions [15]. Various educational and non-educational approaches aiming at preventing postoperative delirium have been implemented and tested in the hospital setting. A controlled study in general-medicine wards showed the effectiveness of the *Hospital Elder Life Program *(HELP) to reduce the rate of delirium by one third in elderly patients [16]. This program had been successfully reproduced in other settings [17,18]. Another randomized study proved the substantial impact of a proactive geriatric consultation preoperatively or within 24 hours postoperatively on severe delirium incidence following hip fracture surgery repair [19]. Although the implementation of a multifaceted intervention would be more effective in preventing delirium than program based on a single component, the value of complex interventions has still not been rigorously assessed [13,14]. The Cochrane advises an assessment of multifaceted intervention using rigorous methodology based on randomized study design [12].

Geriatric pathways have been reinforced since 2002 in France through creation of Mobile Geriatric Teams (MGT) in acute care [20]. The MGT expertise is essential to guaranty appropriate care and improve the management of elderly inpatients. The MGT missions include: a) patient clinical, psychological and social assessments, b) advice, information and training of health care professionals, c) implementation of care and life projects, d) management within the intra-hospital pathways and at the hospital discharge, and e) organization of the outpatient [21,22].

The purpose of this paper is to provide the detailed methodology of the CONFUCIUS stepped wedge trial. The CONFUCIUS trial aims to assess a delirium multifaceted prevention program implemented and coordinated by a MGT. Main objective is to measure the impact of a multifaceted prevention program on the incidence of postoperative delirium in elderly patients. Secondary objectives aim to assess the impact of the program on delirium intensity, postoperative complications, length of hospital stay, and exploring the program feasibility.

## Methods/Design

### Study design

CONFUCIUS protocol is based on a stepped wedge trial design, which is appropriate in assessing the impact of patient safety interventions [23,24]. It is an original design of cluster randomised controlled trial (figure 1). In the CONFUCIUS trial, the multifaceted prevention program will be rolled-out sequentially to three surgical wards (clusters) over four time periods (steps). The order in which the different surgery wards will receive the program is determined at random, allowing the full implementation of intervention in all participating clusters by the end of the trial [24]. Stepped wedge design also has strong methodological value to reduce contamination bias, considering that each cluster acts as its own control and hence provides data in both control and intervention arms of the trial [24].

**Figure 1 F1:**
[figure not shown]
**Design of the CONFUCIUS study**. One cluster (C1, C2 or C3) represents one surgical ward. One unit (control or intervention) represents one time period of one cluster. "White square": "control" unit = surgical wards without multifaceted prevention program "Black square": "intervention" unit = surgical wards with multifaceted prevention program

### Setting and patients

The CONFUCIUS trial will take place in 3 surgical wards (orthopaedic, digestive and urology surgery) of 3 distinct French university hospitals. Each hospital benefits from its own MGT, which is composed of geriatricians and nurses. All health professionals in the participating surgical wards will be involved to conduct the multidisciplinary prevention program (i.e. surgeons, anaesthetists, nurses, and nurse assistants).

Inclusion criteria are age 75 and older, admission for a scheduled surgery (i.e. respectively colorectal cancer, ureterostomy, nephrectomy or cystectomy, total hip or knee replacement), participation agreement and no psychiatric trouble.

### Intervention

The multidisciplinary prevention program will be implemented and coordinated locally by the MGTs (table 1). Within each surgical ward, the components of this program will be introduced simultaneously (figure 2). 1/Preoperative geriatric consultation, 2/Training of the surgical wards staff and implementation of HELP in surgical wards and 3/A periodic morbidity and mortality conference related to delirium cases are detailed below.

**Table 1 T1:** Role of the surgical wards and MGT staff during the CONFUCIUS study

Geriatrician from MGT
Training nurses from surgical wards to the CAM

Training the surgical wards staff o the prevention of postoperative delirium

Perform a preoperative geriatric consultation

Support HELP implementation

Involve a quarterly morbidity and mortality conferences

**Nurse from MGT**

Perform preoperative assessment

Perform MDAS diagnosis for CAM positive patients

**Nurse from the surgical wards**

Perform CAM from the day before the surgery until 7 days after surgery

Involve in HELP implementation

Involve in quarterly morbidity and mortality conferences

**Other medical staff from the surgical wards**

Involve in HELP implementation

Involve in periodic morbidity and mortality conferences

**Figure 2 F2:**
[figure not shown]
**Schema of the management of elderly patients included in the CONFUCIUS study in surgical wards during "control" and "intervention" units**. The specific patient management due to CONFUCIUS study are represented by grey boxes.

#### 1/Preoperative geriatric consultation

Structured geriatric consultation will be performed by geriatricians of the MGT before surgery, including: 1/medical comorbidity assessment; 2/clinical examination, 3/decrease of unnecessary and redundant medications (e.g. anticholinergics, antihistamines); 4/assessment of pain using Numeric Rating Scale (NRS) [25]; 5/assessment of nutritional status using the Mini Nutritional Assessment (MNA) [26]; 6/assessment of self-care functions using Activities of Daily Living (ADL) [27], Instrumental Activities of Daily Living (IADL) [28]and, the "Get-Up and Go" test [29]; 7/assessment of cognitive and depression status using the Mini-Mental State Examination (MMSE) [30] and the Mini Geriatric Depression Scale (Mini-GDS) [31]; 8/delirium assessment using the Confusion Assessment Method (CAM) diagnostic algorithm [32,33] and delirium severity using the Memorial Delirium Assessment Scale (MDAS) [34]. According to the geriatric consultation results and to prevent postoperative confusion, geriatricians will formulate advices on the patient care management during the peroperative period.

#### 2/Training of the surgical wards staff and implementation of the Hospital Elder Life Program (HELP)

All members of medical and nursing staffs will attend a two hours training session performed by the MGTs in their surgical ward. This training will focus on post-operative delirium issues (diagnosis, frequency, seriousness, and risk factors) and the HELP presentation [16]. This non pharmacological program focuses on patient spatiotemporal orientation, including: 1/to promote the use of appropriate glasses and hearing aids; 2/to encourage to bring personal belongings; 3/to encourage proxies to visit the patient during his hospital stay; 4/to set up clocks and calendars in patients room; 5/to adjust the luminosity according on the time of the day; 6/to improve patient implantation in the current reality (for example, telling about the time and the date during medical and nursing cares).

All these recommendations will be reminded by posters on the wall of patient rooms in surgical wards and explained by brochures provided to proxies.

#### 3/Morbidity and mortality conferences related to delirium cases

Morbidity and mortality conference will be organized in surgical ward. On a quarterly basis, they will gather all members of medical and nursing staffs and MGTs to analyze medical records of patients having experienced a postoperative delirium. Their aims are to identify and address the prevention program failures.

### Comparator

Prevention of the postoperative delirium on the control group will be according to usual care of surgical wards (figure 2). Surgical wards staffs will be able to contact the MGT spontaneously, without implementation of any systematic preoperative geriatric consultation, staff training, HELP implementation or morbidity and mortality conference.

### Outcome measurement

The primary outcome of the CONFUCIUS trial is based on postoperative delirium rate within 7 days after surgery. Secondary outcomes are the following: mean delirium intensity, length of hospital stay, postoperative complications 30 days after surgery incidence, mortality 6 months after surgery and feasibility of the multidisciplinary prevention program.

Delirium will be assessed using the CAM, which has been validated in the elderly and is highly sensitive (94-100%) and specific (90-95%) [32,33]. The CAM includes four features: 1) acute onset and fluctuating course, 2) inattention, 3) disorganization of thinking and 4) altered level of consciousness. The diagnosis of delirium requires the presence of features 1 and 2 and either 3 or 4. Its feasibility is good. It can be completed in less than 5 minutes and is well understood by physicians, nurses and trained interviewers. It will be performed by surgical ward nurses from the first to the seventh days after surgery.

Delirium intensity will be assessed using the MDAS (scored 0-30, 30 worst) [34]. The MDAS will be completed by the MGT for all CAM positive patients. Postoperative complications (e.g. pulmonary and cardiac complications, deep vein thrombosis, sepsis, fall, incontinence or retention, pressure ulcer, patient who pull off catheter, infusion and dressing) and length of hospital stay will be collected from medical records.

Compliance of surgical team to the CONFUCIUS program will be assessed for each patient by an external audit. The completion of preoperative consultation file, the appropriate use of glasses and hearing, the presence of personal belongings, clock and calendar in patient room will be checked by a research assistant.

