### Sample size

Sample size calculation was inspired from the methodology of Hussey and Hughes [23] and based on the following hypothesis: 1/three surgical wards (clusters) over four successive time periods, 2/improvement of at least 20% regarding primary outcome after the program implementation (from 60% to 40%) [1,16,19], 3/alpha fixed at 5%, 4/a number of patients per time period ranging from 60 to 120, 5/a coefficient of variation or intracluster correlation coefficient (ICC) ranging from 0 to 0,4. The ICC is a measure of the relatedness of clustered data by comparing the variance within clusters with the variance between clusters. Table 2 presents the statistical power obtained according to various values for ICCs and numbers of patients per time period. At least 90 patients per time period, i.e. 30 per time period and per surgical ward will be necessary to obtain a statistical power greater than 90%. Consequently, 360 patients will be included in the study. The time period duration will be 6 months to ensure the inclusion of 30 patients per time period and per surgical ward.

**Table 2 T2:** Statistical power calculated from intracluster correlation coefficients (ICC) and numbers of patients per time period

ICC	60 patients per time period	90 patients per time period	120 patients per time period
**0**	0.95	0.99	1

**0.1**	0.87	0.96	0.99

**0.2**	0.84	0.95	0.98

**0.3**	0.83	0.94	0.98

**0.4**	0.83	0.94	0.98

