## Discussion

The implementation of the CONFUCIUS program may decrease the occurrence and severity of postoperative delirium leading to the decrease of mortality and postoperative complications in the elderly patients. A decrease of the length of hospital stay may also be disclosed after implementation of the program. The CONFUCIUS study will develop or strengthen the collaboration between surgical wards and MGTs that has already been observed during the preparative time of the study. A better recognition and management of postoperative delirium are expected by surgical ward staffs.

The CONFUCIUS study may have several limitations. Firstly, also the emergency surgery is a risk factor of postoperative delirium, patients admitted for an emergency surgery will not be included in the study. For feasibility reasons, the preoperative geriatric consultation could not be systematically performed in emergency. According to the impact of the multidisciplinary prevention program on postoperative delirium in patients with a scheduled surgery, an adaptation of CONFUCIUS program could be considered for patients admitted via the emergency room. Secondly, the CONFUCIUS program can only be implemented in hospital with MGT and its impact could be linked to MGT performance. However, the geriatric consultation and HELP will be standardized to limit biases.

The CONFUCIUS program associates three complementary interventions focusing on several stages of the patient management: (1) a preoperative geriatric consultation, (2) training of the surgical wards staff with implementation of the HELP, (3) periodic morbidity and mortality conferences. The two first components have been proven individually efficient to prevent postoperative delirium [16,19]. Introduced first in the beginning of the XX^th ^century in USA, morbidity and mortality conference represents a pedagogical method for physicians to analyze and improve health care quality [37,38].

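### Mean delirium intensity is, as far as the text shows, a mean among CAM-positive patients only, a group the programme is meant to change, so the comparison is not like-for-like and could be biased in either direction

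*Protocol article*

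**What the plan says.** The Background section makes intensity an objective in its own right and words it as an effect of the programme: "Secondary objectives aim to assess the impact of the program on delirium intensity". Outcome measurement turns this into an outcome: "Secondary outcomes are the following: mean delirium intensity". The instrument is the MDAS, scored from 0 to 30 with 30 worst.

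The same section then limits who is scored after surgery: "The MDAS will be completed by the MGT for all CAM positive patients". Table 1 repeats the limit among the tasks of the mobile geriatric team nurse: "Perform MDAS diagnosis for CAM positive patients". No score or rank is given to patients who stay CAM-negative.

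Three other places bear on the point:

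- Sample size assumes that the programme lowers the delirium rate from 60% to 40%.
- The Discussion names a second way in which the CAM-positive group may change: "A better recognition and management of postoperative delirium are expected by surgical ward staffs".
- Statistical analysis keeps patients with at least one CAM before and one after surgery. It plans patient-level analyses adjusted for patient characteristics and the ward, and says nothing specific to the MDAS.

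**The concern.** Being CAM-positive within 7 days of surgery is the primary outcome. A mean taken only among CAM-positive patients therefore conditions on an event that occurs after the ward has entered its arm and that the programme is designed to prevent. The delirious patients in the intervention units are those whom the programme failed to protect, and those in the control units are all who would have become delirious under usual care. A difference between the two means mixes any change in severity with a change in who is counted. Adjusting for ward, period or baseline characteristics does not in general undo that selection.

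Detection adds to the problem. Ward nurses perform the CAM, and ward staff are trained on delirium, including its diagnosis, as part of the programme. Mild cases missed in control units may be picked up in intervention units.

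At stake is the answer to a stated secondary objective, and the Discussion's expectation that both the occurrence and the severity of delirium may fall. The primary outcome and the sample size are not affected.

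**Working it through.** **Inputs from the document.** CAM-positive 60% under control and 40% under the programme (Sample size); 360 patients, 30 per ward and period (Sample size); MDAS only in CAM-positive patients (Outcome measurement, Table 1). The article gives no planning figure for intensity, so there is none to reproduce.

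**Assumed.** The article gives no MDAS distribution. For illustration, scores among control cases are taken as uniform from 10 to 25. Remaining cases are taken as unchanged unless stated. A standard wedge is assumed (Figure 1 is not shown), with 6 control and 6 intervention cells.

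**Step 1: who is scored.** Each arm has 6 × 30 = 180 patients. Scored: 0.60 × 180 = 108 control and 0.40 × 180 = 72 intervention patients. A fall from 60% to 40% removes one third of the cases.

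**Step 2: general formula.** Let m be the control mean among cases and p the mean the prevented cases would have had. Then

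remaining mean = (0.60 m − 0.20 p) / 0.40 = 1.5 × (m − p/3).

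This exceeds m when p < m, equals m when p = m, and is below m when p > m. The sign therefore depends only on which cases are prevented.

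**Step 3: numbers.** With m = 17.5, the all-patient control mean, scoring CAM-negative patients 0, is 0.60 × 17.5 = 10.5.

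| Cases prevented | p | CAM-positive mean, programme | Change from 17.5 | All-patient mean, programme |
|---|---|---|---|---|
| Mildest third (10–15) | 12.5 | 1.5 × (17.5 − 4.17) = 20.0 | +2.5 | 0.40 × 20.0 = 8.0 |
| Unrelated to severity | 17.5 | 1.5 × (17.5 − 5.83) = 17.5 | 0 | 0.40 × 17.5 = 7.0 |
| Most severe third (20–25) | 22.5 | 1.5 × (17.5 − 7.5) = 15.0 | −2.5 | 0.40 × 15.0 = 6.0 |

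No remaining patient's severity changes in any row, yet the CAM-positive comparison reads as harm, no effect or benefit. The all-patient mean falls in all three.

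**Step 4: other assumed distributions.** With normal distributions truncated to 0–30 (mean/SD 12/4, 15/5, 18/5), preventing the mildest third moves the CAM-positive mean from 12.0 to 14.2, 15.0 to 17.7 and 17.9 to 20.6, a rise of 2.2 to 2.7 points. Preventing the most severe third lowers it by about the same amount. Prevention only graded towards mild cases gives a rise of 1.1 to 1.4.

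For scale, in the 15/5 case the SD after truncation is 4.93. Ignoring clustering and using that SD in both groups, z = 2.70 / (4.93 × √(1/108 + 1/72)) = 2.70 / 0.75 = 3.6. The graded pattern gives about 1.9.

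**Step 5: changed detection.** If the programme has no real effect but an extra 5% of patients are found as mild cases (mean 12.5), the CAM-positive mean becomes (0.60 × 17.5 + 0.05 × 12.5) / 0.65 = 17.1, an apparent benefit of 0.4. The truncated normals give 0.3 to 0.4.

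**Step 6: every patient improves.** Suppose a normal latent severity shifts down equally in all patients, taking the share above the CAM threshold from 60% to 40%. The normal quantile for 60% is 0.253, so the true shift is 2 × 0.253 = 0.51 SD. The mean excess over the threshold among positives falls only from 0.90 to 0.71 SD. The direction is right, but the size is well short of the true shift.

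**The case against.** **The denominator is not stated.** The text says who is scored, not who is averaged, and the analysis set is defined by CAM availability with no MDAS subset. A condensed article may leave the denominator to a fuller document. It is correct that the restriction of the mean is an inference. But the article does fix the scoring rule, in two places, and pairs it with a mean. As written, that leads to a mean among CAM-positive patients. Any other reading needs a value for CAM-negative patients, which the article does not give. The MDAS in the preoperative geriatric consultation does not supply one, because it precedes surgery and belongs to the intervention only.

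**The direction is open.** A reader might infer that the programme would look harmful on severity. The document does not support that. Apparent harm requires prevented cases to be milder than average and the others unchanged. Prevention unrelated to severity produces no shift, and preventing severe cases or detecting more mild ones flatters the programme. This objection stands in full, and the point is limited accordingly.

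**An all-patient measure answers a different question.** This stands in part. In the mildest-third example the odds ratio for any delirium is (0.60/0.40) / (0.40/0.60) = 2.25. For any MDAS cut m of 15 or more, the share of all patients above it is 0.60 × (25 − m)/15 = 0.04 × (25 − m) under control and 0.40 × (25 − m)/10 = 0.04 × (25 − m) under the programme, an odds ratio of 1. Proportional odds fails there, and the whole apparent gain comes from incidence. The model can be only one option, and the result must be read as incidence and severity combined.

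**Importance.** Intensity comes first in the list of secondary objectives, but no hierarchy is stated, so list order gives it no special rank.

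**Conclusion.** The point holds in this form: as far as the text shows, mean delirium intensity is a mean among patients who became delirious. The programme is meant to shrink that group by a third and may change how its members are detected. The between-arm difference is then not a like-for-like estimate of an effect on severity, and its bias has no known sign.

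Under the assumed uniform distribution the artefact ranges from −2.5 to +2.5 points on the 30-point scale; the truncated normals give up to about 2.7 in either direction. These sizes rest on invented MDAS distributions, on sharp selection of the mildest or most severe third, and on unchanged remaining cases. Weaker selection gives less, and none at all if prevention is unrelated to severity. The sizes show what is possible and are not a forecast. The weakness itself rests only on the scoring rule and the planned change in incidence. It should be put right before severity is compared between arms.

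**What to change.** State the denominator. Define the comparative severity outcome on all analysed patients, with CAM-negative patients given the lowest rank (or a stated score of 0, declared as a convention). Compare the arms with a rank-based or ordinal analysis that has ward, period and intervention terms. A proportional-odds model is one option, provided its assumption is checked.

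Show the distribution over severity categories, including no delirium, in each arm, so that readers can see whether a difference comes from fewer cases or from milder ones. Report the mean MDAS among CAM-positive patients as descriptive only, with a sentence saying that it does not estimate an effect of the programme.

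The cost is wording: the CAM is already planned for the first to seventh days after surgery, so no new data are needed. Two limits should be stated. The all-patient outcome overlaps with the primary outcome and combines incidence with severity. It also does not remove a change in detection: in Step 5 the all-patient mean would rise from 10.5 to 10.5 + 0.05 × 12.5 = 11.1 with no real change in patients.
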